12. Blood biochemistry: Liver function (TP, A, G, ALT, AST, LDH, ALP, TBil, DBil, and IBil), renal function (BUN, Cr, and UA), blood lipid tetrachoric (TC, TG, HDL, and LDL), electrolytes (K+, Na+, CL-, Ca2+, Mg2+, and P), lipase, amylase, fasting glucose, etc. are performed within 7 days before enrollment, at C1D7, C1D21, and thereafter at days 21 of every two cycles (odd numbered cycles), and at dropout visit, and at days 21 after treatment; During the drug administration, patients who develop early symptoms of liver injury (e.g., appetite loss, vomiting, right upper abdominal discomfort, malaise, etc.) before blood biochemical abnormalities should undergo blood biochemistry immediately. If ALT or AST is up to 3 times ULN or baseline value and total bilirubin up to 2 times the ULN or baseline value, the frequency of tests should be increased (recommended 1-2 times/week);
13. Coagulation function (PT, APTT, TT, Fbg, and INR) are performed within 7 days before enrollment, at C1D7, C1D21, and thereafter at days 21 of every two cycles (odd numbered cycles), and at dropout visit.
14. Thyroid function (T3, T4, FT3, FT4, and TSH) are performed within 7 days before enrollment, at C1D7, C1D21, and thereafter at days 21 of every two cycles (odd numbered cycles), and at dropout visit.
15. 12-ECG are performed within 7 days before enrollment, at C1D7, C1D21, and thereafter at days 21 of every two cycles (odd numbered cycles), and at dropout visit. If an abnormal ECG is identified, two additional confirmations must be performed (each 5 minutes apart and the QTc interval should be indicated);
16. Myo-cardial enzymonram is detected within 7 days before enrollment. This examination is supplemented only when symptoms such as precordial pain, palpitations, and ECG abnormalities are present;
17. Echocardiography is performed within 7 days before enrollment and at dropout visit. This examination is supplemented only when clinically meaningful ECG abnormalities occur during treatment;
18. Hepatitis B virus (HBV) and hepatitis C virus examination: HBV examination (HBsAg, HBsAb, HBeAg, HBeAb, and HBcAb) is performed and if the test result is abnormal, viral replication (HBA DNA) and hepatitis C virus antibody (anti-HCV) test should be conducted;
19. Pregnancy testing is limited to women of childbearing age, who are required to undergo a pregnancy test within 7 days before enrollment;

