Subjects should be cautiously given CYP3A inducers (carbamazepine, rifampicin); phenobarbital inhibitors (ketoconazole, itraconazole, erythromycin, and clarithromycin); CYP3A4 substrate (simvastatin, cyclosporine, and piperidine); other medications metabolized by CYP3A4 (benzodiazepines, dihydropyridine calcium antagonist [calcium antagonism may be selected as appropriate for uncontrolled ACEI hypertension]; HMG-COA reductase inhibitor); CYP2C9 substrate (diclofenac, phenytoin sodium, piroxicam, S-warfarin, and tolbutamide); CYP2C19 substrate (diazepam, imipramine, lansoprazole, and S-mephenytoin). Use CYP2C9 and CYP2C19 substrates with caution, as detailed in the table below.

| P450 enzymes | Substrate |
| --- | --- |
| CYP2C9 | diclofenac, phenytoin sodium, piroxicam, S-warfarin, and tolbutamide |
| CYP2C19 | diazepam, imipramine, lansoprazole, and S-mephenytoin |

Citrus, star fruit, grapefruit, and grapefruit juice affect cytochrome P450 activity and should be avoided in combination.

Since Tinib-related drugs have the side effects of prolonging QT interval in clinical practice, it is necessary to use drugs that prolong QT interval with caution during the trial. This includes, but is not limited to, the several classes of medicines listed below:

- Antimicrobials (clarithromycin, azithromycin, erythromycin, roxithromycin, metronidazole, moxifloxacin);
- Antiarrhythmic drugs (quinidine, sotalol, amiodarone, disopyramide, procaine amide);
- Antipsychotics (risperidone, fluphenazine, haloperidol, haloperidol, thioridazine, pimozide, olanzapine, clozapine);
- Antifungal drugs (fluconazole, ketoconazole);
- Antimalarial drugs (mefloquine, chloroquine);
- Antidepressants (amitriptyline, imipramine, clomipramine, dosulepin, doxepin).
  - 1. **Permitted Concomitant Medications**

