(2) If DLTs are reported in one of three patients, three additional patients are enrolled at the same dose level (12 mg); if no additional DLT occurr in these three patients, the stage 2 study will be conducted at the dose of 12 mg anlotinib; if DLTs are reported in ≥1 of three patients, the stage 2 study will be conducted at the dose of 10 mg anlotinib.

(3) If DLTs are reported in ≥2 of three patients, the stage 2 study will be conducted at the dose of 10 mg anlotinib.

Subjects enrolled in the 3+3 dose escalation trial receive the same examinations and follow-up to those in stage 2, as detailed in the flow chart in the stage 2 study of anlotinib.

[figure not shown]

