12. Blood biochemistry: Liver function (TP, A, G, ALT, AST, LDH, ALP, TBil, DBil, and IBil), renal function (BUN, Cr, and UA), blood lipid tetrachoric (TC, TG, HDL, and LDL), electrolytes (K+, Na+, CL-, Ca2+, Mg2+, and P), lipase, amylase, fasting glucose, etc. are performed within 7 days before enrollment, at C1D7, C1D21, and thereafter at days 21 of every two cycles (odd numbered cycles), and at dropout visit, and at days 21 after treatment; During the drug administration, patients who develop early symptoms of liver injury (e.g., appetite loss, vomiting, right upper abdominal discomfort, malaise, etc.) before blood biochemical abnormalities should undergo blood biochemistry immediately. If ALT or AST is up to 3 times ULN or baseline value and total bilirubin up to 2 times the ULN or baseline value, the frequency of tests should be increased (recommended 1-2 times/week);
13. Coagulation function (PT, APTT, TT, Fbg, and INR) are performed within 7 days before enrollment, at C1D7, C1D21, and thereafter at days 21 of every two cycles (odd numbered cycles), and at dropout visit.
14. Thyroid function (T3, T4, FT3, FT4, and TSH) are performed within 7 days before enrollment, at C1D7, C1D21, and thereafter at days 21 of every two cycles (odd numbered cycles), and at dropout visit.
15. 12-ECG are performed within 7 days before enrollment, at C1D7, C1D21, and thereafter at days 21 of every two cycles (odd numbered cycles), and at dropout visit. If an abnormal ECG is identified, two additional confirmations must be performed (each 5 minutes apart and the QTc interval should be indicated);
16. Myo-cardial enzymonram is detected within 7 days before enrollment. This examination is supplemented only when symptoms such as precordial pain, palpitations, and ECG abnormalities are present;
17. Echocardiography is performed within 7 days before enrollment and at dropout visit. This examination is supplemented only when clinically meaningful ECG abnormalities occur during treatment;
18. Hepatitis B virus (HBV) and hepatitis C virus examination: HBV examination (HBsAg, HBsAb, HBeAg, HBeAb, and HBcAb) is performed and if the test result is abnormal, viral replication (HBA DNA) and hepatitis C virus antibody (anti-HCV) test should be conducted;
19. Pregnancy testing is limited to women of childbearing age, who are required to undergo a pregnancy test within 7 days before enrollment;

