12-ECG: During the screening period, the results of 12-ECG within 7 days before enrollment are allowed. Results within ±7 days of study completion/withdrawal are allowed at the last visit. Reports of 12-ECG must maintain traceability. The thermal sensitivity spectrum should clearly record the name and examination time of subjects. Copies of the bedside ECG spectra are reserved for reference but not included in statistical analysis.

Echocardiography: During the screening period, the results of echocardiography within 14 days before enrollment are allowed. Left ventricular ejection fraction is a mandatory item.

Myo-cardial enzymonram (CK, CK-MB) and troponin: During the screening period, the results of Myo-cardial enzymonram and troponin within 7 days before enrollment are allowed. This examination is supplemented only when symptoms such as precordial pain, palpitations, and clinically significant ECG abnormalities are presen.

- - 1. Imaging examination

Sites: During the screening period, head, neck, chest, and abdomen (including pelvic) are the mandatory sites that need to be examined. Other sites should be determined based on the trial protocol and clinical judgment.

Method: CT or MRI. MRI is used for head and neck (CT can be used as a substitute for MRI in subjects with contraindications for MRI). CT or MRI is used for chest and abdomen. Bone scan (ECT) is required if suspected bone metastasis.

Requirement for examination: The imaging examination should be performed under the same conditions as the baseline. Imaging examinations are performed as per RECIST v1.1 criteria to ensure a reasonable evaluation of efficacy.

Time requirements: During the screening period, ECT results of bone metastasis within 3 months before enrollment are allowed, while CT/MRI results of other sites within 28 days before enrollment are allowed. 6.2.4 Imaging within ±28 days of study completion/withdrawal are allowed at the last visit. After enrollment, all subjects were recommended to undergo ECT re-examination every 6 months. Subjects with baseline bone metastases were required to evaluate the bone metastasis site at each imaging evaluation. If investigator suspects new lesions based on clinical symptoms, confirmed ECT/MRI/CT are required.

- - 1. Detection of EGFR mutation, tumor mutation burden (TMB) and PD-L1 expression

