Subjects who have received treatment with first or second-generation EGFR TKIs are required to provide a genetic testing report, proving the absence of primary or acquired *T790M* mutations. Subjects who have received treatment with third-generation EGFR TKIs are required to provide a genetic testing report, proving the positivity of EGFR mutations. For subjects with access to tissue samples, it is recommended to prioritize tissue-based *EGFR* mutation testing. Subjects without access to tissue samples may choose blood-based *EGFR* mutation testing using traditional gene testing (such as ddPCR, Arms-PCR, etc.) or high-throughput sequencing. T790M mutation and Exon 20 insertion mutation are key sites for testing.

PD-L1 expression is measured in suitable subjects from sub-centers with testing conditions.The selected subjects should meet the criteria for biopsy, and it is anticipated that sufficient tissue will be obtained for immunohistochemistry. Fresh tissue is divided into two parts, with one directly used for the immunohistochemistry of PD-L1, and the other prepared into a paraffin block for TMB testing.

- 1. Maximum tolerated dose and dose-limiting toxicity

MTD: Toxicity and safety are observed to determine the MTD of anlotinib when combined with TQB2450. MTD is defined as the highest dose when less than 33% of subjects experienced DLT.

DLT: DLT is defined as any one of the following toxicities occurring within the first 21 days of treatment (including events that started in the first cycle but were confirmed in the second cycle), as per NCI CTCAE 5.0.

1. Grade IV hematologic toxicity and following events:
2. ≥ CTCAE grade 3 febrile neutropenia (ANC<1000/ul; body temperature ≥38.5°C)
3. ≥ CTCAE grade 3 neutropenia lasting for >7 days
4. CTCAE grade 3 platelet count decreased lasting for >7 days, with signs of clinically significant bleeding or need for platelet transfusion
5. Grade II or higher liver and kidney dysfunction (lasting for >7 days after symptomatic treatment) and following events:
6. CTCAE grade 2 bilirubin increased, lasting for >7 days
7. ≥ CTCAE grade 3 bilirubin increased
8. CTCAE grade 3 AST or ALT increased, lasting for >7 days
9. CTCAE grade 4 AST or ALT increased
10. Grade III or higher non-hematologic toxicity (except for alopecias) and following events:
11. ≥CTCAE grade 2 pancreatitis
12. Cerebral hemorrhage, ≥grade 2 pulmonary hemorrhage
13. grade 2 abnormal coagulation or bleeding, lasting for >7 days

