**8.2.5 Safety analyses**

Safety analysis includes AEs/adverse reactions, serious AEs/adverse reactions, laboratory tests, vital signs, physical examination, ECOG score, 12-lead electrocardiogram.

- - - 1. **AEs**

Medical coding of adverse events/adverse reactions/immune-related adverse events was performed with the use of MedDRA 21.0. The occurrence of adverse events/adverse reactions/immune-related adverse events, serious adverse events/adverse reactions/immune-related adverse events, adverse events/adverse reactions/immune-related adverse events leading to withdrawal, and adverse events/adverse reactions/immune-related adverse events leading to death were summarized, the number and times of occurrence were listed, and the incidence was calculated. The incidence of adverse events/adverse reactions/immune-related adverse events and serious adverse events/adverse reactions were summarized according to system organ classification (SOC) and preferred terminology (PT), and the number and incidence of adverse events/adverse reactions were listed. The association and toxicity grade of AEs/AEs (NCI CTCAE v5.0) were summarized according to SOC and PT, and the number and incidence of AEs/AEs were listed. The list describes the details of the occurrence of each adverse event/adverse reaction for each subject.

- - - 1. **Laboratory tests**

The laboratory tests were classified according to clinical significance, namely normal, abnormal without clinical significance, abnormal with clinical significance or normal and abnormal. The laboratory tests were summarized descriptively by frequency and percentage using cross-classification table.

Lists describe occurrences of normal before treatment but abnormal after treatment, as well as subjects who were abnormal before treatment but worsened after treatment. The mean, standard deviation, median, quartile, minimum and maximum values of routine blood test, blood biochemistry, four coagulation tests, thyroid function, lipase and amylase were listed. The measured values and changes before and after treatment were described. Paired *t* tests were performed when necessary.

Describe the proportion of subjects with abnormal changes who have “abnormal clinical significance”, in which the investigator judges whether the abnormality has clinical significance.

| Type | Tests |
| --- | --- |
| Hemanalysis | WBC, ANC, LYM, RBC, Hb, PLT |

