| Urinalysis | urine RBC, urine WBC, proteinuria, glucose in urine (proteinuria ≥ 2+, additional 24-h urine protein quantification is required within 1 week) |
| Stool tests | leukocyte, RBC, occult blood |
| Blood biochemistry | ALT, AST, GGT, ALP, LDH, TP, ALB, TBIL, DBIL, GLU, BUN/Urea, Cr, K^+^, Na^+^, Cl^-^, Ca^2+^, Mg^2+^, P, TC, TG, HDL, LDL |
| Six coagulation tests | INR, APTT, PT, FIB, TT, D-D dimer |
| Lipase | lipase |
| Amylase | amylase |
| Tumor marker | carcinoembryonic antigen |
| Pregnancy text | human chorionic gonadotophin |
| Epidemiological | HbsAgn (Additional HBV DNA if positive), HBsAb, HBeAg, HBeAb, HBcAb, Anti-HCV, HIV |

- - - 1. **Physical examination**

The physical examination was classified according to normal and abnormal, and the cross-classification table was used. Frequency and percentage were used to summarize the physical examination descriptively.

- - - 1. **Vital signs**

Means, standard deviations, medians, quartiles, and minimum and maximum values will be listed for vital signs, describing the measurements and changes before and after treatment. Paired *t* tests were performed when necessary.

- - - 1. **12-lead electrocardiogram**

The 12-lead electrocardiogram was classified according to clinical significance, namely normal, abnormal without clinical significance, abnormal with clinical significance or normal and abnormal. The 12-lead electrocardiogram was summarized descriptively by frequency and percentage using cross-classification table.

- - - 1. **Concomitant medications**

The WHODrug was used to code the combined drugs, and the use of combined drugs during the study period and the frequency of each drug were summarized. The details of the combined drugs are listed.

- - 1. **Efficacy analysis**
       1. **Analysis of primary efficacy endpoints**

PFS is defined as the time from enrollment to the first time of disease progression or death from any cause, whichever occurs first.

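### QT prolongation is named as a drug risk, but QTc is required only after an abnormal ECG, so a patient with a normal screening ECG has no required baseline QTc and the ECG table cannot show a QTc change

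*Protocol*

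**What the plan says.** The risk is stated in protocol section 5.6, in the part on prohibited or cautiously used co-medication: "Since Tinib-related drugs have the side effects of prolonging QT interval in clinical practice". The action attached to it is caution with a list of QT-prolonging drugs. They are not banned, so a patient may take them together with anlotinib.

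The visit schedule (Study Procedures, repeated in section 6.1) places a 12-lead ECG at screening, C1D7, C1D21, day 21 of later odd-numbered cycles and the withdrawal visit. Phase I patients follow the same schedule: "Subjects enrolled in the 3+3 dose escalation trial receive the same examinations and follow-up to those in stage 2". Footnote 15, worded identically in both schedules, says when QTc is needed: "If an abnormal ECG is identified, two additional confirmations must be performed (each 5 minutes apart and the QTc interval should be indicated". No other part of the protocol requires a QTc value.

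For the analysis, section 8.2.5 classifies each ECG as normal or abnormal, with or without clinical significance, and continues: "The 12-lead electrocardiogram was summarized descriptively by frequency and percentage using cross-classification table". In the same section, laboratory tests and vital signs also receive measured values and before-to-after changes.

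**The concern.** QTc is a continuous measurement, and its drug effect is read as a change from the patient's own starting value. In a single-arm trial that starting value is the only internal comparator. If it need not be recorded, a QTc found on treatment cannot reliably be separated from one that was already long at entry.

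The category table does not fill the gap. A move from normal to abnormal does not say that QTc was the reason or how far it moved. A rise that leaves the tracing in the same category does not appear at all.

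What is at stake is the description of one named safety risk of a new combination, including at the phase I dose steps. No efficacy conclusion depends on it.

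**Working it through.** No figure in the protocol needs reproducing, and no arithmetic settles the point. It turns on what the text requires for each kind of patient.

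**Inputs**
- Footnote 15: ECG timing, and QTc on the two repeats after an abnormal tracing.
- Section 6.2, cardiac function examination: a time window and traceability for ECG reports, with no interval named. For echocardiography the same section makes ejection fraction a mandatory item, so the protocol does name a required parameter where it wants one.
- Eligibility criteria, the DLT list in section 6.3 and the anlotinib dose tables in section 5.5: none mentions QTc.
- Section 8.2.5: ECG by category only; laboratory tests and vital signs by value and change as well.

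**Required QTc values, by patient**

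| Screening ECG | On-treatment ECGs | Required baseline QTc | Required on-treatment QTc | Change from baseline from required data |
| --- | --- | --- | --- | --- |
| Normal | All normal | None | None | Not available |
| Normal | One or more abnormal | None | On two repeats per abnormal ECG | Not available |
| Abnormal | All normal | On two repeats | None | Not available |
| Abnormal | One or more abnormal | On two repeats | On two repeats per abnormal ECG | Available at the abnormal visits |

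Only the last row yields a change from baseline from required data, and only at visits where the ECG again reads as abnormal. The first two rows cover every patient who enters with a normal ECG.

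**What other parts of the protocol still catch**
- Section 8.2.5, adverse events: "The association and toxicity grade of AEs/AEs (NCI CTCAE v5.0) were summarized according to SOC and PT", with a listing for each patient.
- Section 6.3, dose-limiting toxicity: "Grade III or higher non-hematologic toxicity (except for alopecias) and following events". A QT event judged to be grade III or higher falls under this general heading.
- Table 5.5-9: for other non-hematologic toxicities, grade 2 or 3 leads to delay and one dose level down, and grade 4 ends treatment.

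These routes start once an abnormality has been noticed and judged an adverse event. They do not supply a baseline value, and they do not describe change in patients whose tracings are read as normal.

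**The case against.** The strongest reply is that this belongs to the statistical analysis plan and the eCRF, neither of which is shown. QTc by visit and change from baseline are ordinary table detail. Section 8.2.5 does not call the cross-table the only ECG output. Section 8.2 already sets summary statistics for quantitative variables, which would cover QTc wherever it is recorded. This stands for the table taken alone. It does not answer footnote 15, which is a collection rule in the protocol: a later table or a general summary rule can use only values that sites have recorded.

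A second reply is that the QT remark is a class-level sentence in the co-medication section. QT prolongation is not among the common anlotinib events given management guidance in section 6.5, and no QT objective or endpoint exists. That is fair, and it is a reason to keep the point minor.

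Three stronger readings are tempting and are not supported:
- A reader might infer that QTc will not be recorded on routine tracings. Footnote 15 sets a minimum and does not forbid it; sites may record QTc anyway, though optional recording across centres can leave baselines incomplete.
- A reader might infer that QT risk goes unmonitored. The adverse event, dose-limiting toxicity and dose-adjustment routes above show otherwise.
- A reader might take a sentence in section 6.2, "Copies of the bedside ECG spectra are reserved for reference but not included in statistical analysis", as removing the screening tracing from later use. It concerns copies of bedside tracings and does not clearly cover the scheduled ECGs, which section 8.2.5 includes in the safety analysis. The point does not rest on it.

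**Conclusion.** The point holds as a minor one and is best treated as a cheap improvement. The protocol names a QT risk and already takes the tracings, but it does not require the measurement that would show the risk. A patient with a normal screening ECG has no required baseline QTc, and the stated ECG table cannot show a QTc change or its size.

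The gap is limited to systematic description of QTc change: rises on tracings still read as normal, and values on repeat tracings that lack a required comparator. No number of missed cases follows, because the protocol gives neither a rate of abnormal ECGs nor a rate of QTc prolongation, and none is assumed here. The progression-free survival analysis and the 3+3 decision rules are unaffected as written.

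The conclusion assumes that QTc in footnote 15 attaches to the repeat tracings, as its wording says, and that no data-collection instruction outside the protocol already requires QTc at every ECG.

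**What to change.** **Footnote 15, in both schedules.** Require the QTc interval on every scheduled 12-lead ECG, including screening. Name one QT correction formula for use at all centres, so that changes from baseline do not mix formulas. Keep the two repeat tracings after an abnormal ECG.

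**Section 8.2.5.** Keep the cross-table. Add QTc value and change from baseline by visit, and the number and percentage of patients by worst post-baseline QTc according to CTCAE v5.0 grade, the grading system the protocol already uses.

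**Cost.** One eCRF field per scheduled ECG and one extra table. The tracings are already planned, so patients undergo no added procedure.

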14. CTCAE grade 3 fatigue, lasting for >7 days
15. CTCAE grade 3 hypertension, hand-foot skin reaction, diarrhea, nausea, and vomiting that are not relieved by symptomatic treatment until the next treatment cycle.
16. CTCAE grade 3 abnormal laboratory examinations that are not relieved by symptomatic treatment until the next treatment cycle.

If one subject experiences toxicity that met the criteria for DLT, the study treatment was interrupted and follow-up was performed as described in the study procedures. Treatment can be discontinued due to any DLT. However, under the investigator and co-sponsor approval, subjects with DLT could receive the next lowest dose level after recovery.

- 1. Efficacy assessment
     1. Primary endpoint
- **Progression-free survival:**

PFS is defined as the time from enrollment to the first time of PD or death from any cause, whichever occurs first.

If the subject did not experience disease progression or death, PFS is defined as the date of the last confirmed progression-free. Subjects who discontinued for reasons other than disease progression (no subsequent tumor imaging assessment) and starting subsequent therapy after the trial were censored at the time of discontinuation or the initiation of subsequent therapy. In cases other than those described above, pre-planned sensitivity analyses will undertake to define PFS based on the date of confirming imaging progression events. New onset other tumor is not considered indicative of PD and is not censored as data.

If the image examination and assessment show PD, the date of PD is not defined as the imaging time of first signs of PD, but the time of definite imaging evidence of PD. If the PD is diagnosed with other clinical examinations, the date of PD is defined as the diagnosis time.

- - 1. Secondary endpoints
- **OS:** OS is defined as the time from enrollment to the date of death due to any cause. For the analysis of OS, data for patients who are alive will be censored for OS at the time of the last follow-up. Data for patients who were lost to follow-up will be censored for OS at the last date they were known to be alive. Censored OS is defined as the time from randomization to censor.
- **1-year PFS rate:** 1-year PFS rate is defined as the percentage of patients who have not progressed or died at 1 year.
- **1-year OS rate:** 1-year OS rate is defined as the percentage of patients who are still alive at 1 year.

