- **Duration of response (DOR):** DOR is defined as the time from first documented evidence of complete response (CR) or partial response (PR) until PD or death, whichever occurred first. For the analysis of DOR, data for patients who discontinue study due to due to reasons other than disease progression (without subsequent imaging examinations) or hose who received post-trial treatment will be censored at the time of study discontinuation or the initiation of post-trial treatment. The occurrence of newly developed other tumors is not considered as a PD event, and will be not censored.
- **Disease control rate (DCR):** DCR is defined as the percentage of subjects with PR, CR, or stable disease (SD) lasting for ≥4 weeks.
- **Objective response rate (ORR):** ORR is defined as the percentage of subjects with confirmed tumor volume reduction to pre-specified values and maintenance of minimum time requirements (≥4 weeks), including subjects with a PR or CR. Objective responses are assessed per RECIST v1.1. Subjects must have at least one measurable lesion at baseline. The response was classified as CR, PR, SD, and PD according to RECIST v1.1.
  1. Safety assessment
     1. Safety management

Various management will be taken to ensure the safety of subjects in the study, including strict inclusion and exclusion criteria and close monitoring (hospitalization monitoring, follow-up, and out-of-hospital diary card recording and telephone follow-up).

Safety is analyzed in the safety analysis set (SAS).

- - 1. Adverse events

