If the subject did not experience disease progression or death, PFS is defined as the date of the last confirmed progression-free. Subjects who discontinued for reasons other than disease progression (no subsequent tumor imaging assessment) and starting subsequent therapy after the trial were censored at the time of discontinuation or the initiation of subsequent therapy. In cases other than those described above, pre-planned sensitivity analyses will undertake to define PFS based on the date of confirming imaging progression events. New onset other tumor is not considered indicative of PD and is not censored as data.

If the image examination and assessment show PD, the date of PD is not defined as the imaging time of first signs of PD, but the time of definite imaging evidence of PD. If the PD is diagnosed with other clinical examinations, the date of PD is defined as the diagnosis time.

- - - 1. **Analysis of secondary efficacy endpoints**

OS is defined as the time from enrollment to the date of death due to any cause. For the analysis of OS, data for patients who are alive will be censored for OS at the time of the last follow-up. Data for patients who were lost to follow-up will be censored for OS at the last date they were known to be alive. Censored OS is defined as the time from randomization to censor.

One-year progression-free rate is defined as the probability of patients experiencing the endpoint events of disease progression from enrollment to one year. Endpoint events include disease progression, death, and withdrawal due to intolerance.

One-year survival rate is defined as the probability of patients experiencing the endpoint event of death from enrollment to one year.

DOR is defined as the time from the date of CP and PR until the date of disease progression. Subjects who discontinued for reasons other than disease progression (no subsequent tumor imaging assessment) and starting subsequent therapy after the trial were censored at the time of discontinuation or the initiation of subsequent therapy. New onset other tumor is not considered indicative of PD and is not censored as data.

DCR is defined as the percentage of subjects with PR, CR, or SD lasting for ≥4 weeks.

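### For secondary endpoints, section 8.2 contradicts section 6.4: intolerance withdrawal becomes a 1-year progression-free-rate event, death drops out of duration of response, and both 1-year rates are worded as event probabilities

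*Protocol*

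**What the plan says.** Section 6.4 (Efficacy assessment) sets the definitions:

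- For the primary endpoint: "PFS is defined as the time from enrollment to the first time of PD or death from any cause, whichever occurs first".
- For PFS at the 12-month landmark, among the secondary endpoints: "1-year PFS rate is defined as the percentage of patients who have not progressed or died at 1 year".
- For how long a response lasts: "DOR is defined as the time from first documented evidence of complete response (CR) or partial response (PR) until PD or death".
- For survival at the 12-month landmark, in the same list: "1-year OS rate is defined as the percentage of patients who are still alive at 1 year".

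Under the PFS rule in section 6.4, subjects who discontinue for a reason other than progression are censored if no later tumour imaging exists. The rule also names the start of subsequent therapy as a censoring point. The notes to the study procedures table ask that patients who stop without imaging progression, intolerance included, go on being imaged until progression, other anticancer therapy, death or the end of the study.

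Section 8.2 repeats the PFS definition and censoring rule under its primary endpoint heading. Under its secondary endpoint heading it departs from section 6.4:

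- For the 12-month progression-free landmark: "One-year progression-free rate is defined as the probability of patients experiencing the endpoint events of disease progression from enrollment to one year". It goes on to list what counts as an event for this rate: "Endpoint events include disease progression, death, and withdrawal due to intolerance".
- For the 12-month survival landmark, the wording is again that of an event probability: "One-year survival rate is defined as the probability of patients experiencing the endpoint event of death from enrollment to one year".
- For how long a response lasts, death is no longer named: "DOR is defined as the time from the date of CP and PR until the date of disease progression".

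The closing Kaplan-Meier paragraph of section 8.2 says that a 1-year disease progression rate and a 1-year survival rate will be estimated.

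**The concern.** Two of the three differences change what is estimated.

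First, a patient who withdraws for intolerance counts as a failure in the 1-year progression-free rate. In the PFS analysis the same patient is either censored or still at risk. The median PFS and the 1-year rate, reported side by side, would come from different event sets. The added event is also loosely defined: section 5.5 lets a patient who permanently stops one drug for toxicity continue the other, and section 8.2 does not say whether that counts as withdrawal.

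Second, under section 8.2 a responder who dies without documented progression has no DoR event, and no rule says what happens instead.

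The third difference is one of wording: both 1-year rates are described as the chance of having the event, the opposite of their labels and of section 6.4.

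The trial is single-arm and read against historical data. Two conflicting definitions in one protocol leave room to choose between them after the results are seen.

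**Working it through.** **Do these definitions touch the plan's own figures?** Inputs from section 8.2.1 and the sample size section: median 9 months against 5 months, two-sided alpha 0.05, power 0.90, 20% loss, 54 patients, 32 events, 24 months in total with 12 months of accrual.

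- Events needed, one-sample exponential test: (1.960 + 1.282)² / ln(9/5)² = 30.4.
- Hazard λ = ln 2 / 9. With uniform accrual, P(event) = 1 − (e^(−12λ) − e^(−24λ)) / (12λ) = 0.741.
- Expected events: 54 × 0.80 × 0.741 = 32.0, as stated.

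The plan's figures are reproduced with PFS alone and do not depend on the secondary definitions.

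**Intolerance as an event.** Assume exponential PFS with the 9-month median.

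- S(12) = exp(−ln 2 × 12/9) = 0.3969, or 39.7% event-free under section 6.4.
- Let q be the net probability of intolerance withdrawal by 12 months (its probability if progression and death did not intervene), independent of PFS. The event-free rate is then S(12) × (1 − q).

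| q (assumed) | Calculation | 12-month event-free rate |
| --- | --- | --- |
| 0 | 0.3969 | 39.7% |
| 5% | 0.3969 × 0.95 | 37.7% |
| 10% | 0.3969 × 0.90 | 35.7% |
| 20% | 0.3969 × 0.80 | 31.7% |

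q is not the share of patients seen to withdraw, because a patient who progresses first can no longer do so. For q = 10% the withdrawal hazard is −ln(0.90)/12 = 0.00878 per month and the PFS hazard is 0.0770. The observed share by 12 months is 0.00878/(0.0770 + 0.00878) × (1 − 0.357) = 6.6%. For a given observed share, the drop is therefore somewhat larger than the table suggests.

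**Direction of the rates.** The complement of S(12) is 1 − 0.397 = 60.3% at the 9-month median. At the 5-month historical median, S(12) = exp(−ln 2 × 12/5) = 18.9%, with complement 81.1%.

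**Duration of response.** No arithmetic is possible, since the protocol gives no rate of death in response. Section 6.4 ends DoR at progression or death; section 8.2 ends it at progression and names censoring for other discontinuations and later therapy, but is silent on death. If such deaths are censored, the Kaplan-Meier DoR is biased upward relative to the section 6.4 endpoint.

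**The case against.** The strongest reply is that nothing decisive is affected. Section 3.2 bases a positive outcome on PFS, and the primary PFS definition is the same in sections 6.4 and 8.2. A reader might infer that section 8.2 makes intolerance a PFS event in the primary analysis. It does not: the sentence belongs to the 1-year progression-free rate only. The synopsis does list DoR and the 12-month PFS rate under its primary effect endpoints, but sections 6.4 and 8.2 treat them as secondary. This part of the reply stands, and it limits the weight of the point.

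A second reply is that the inverted wording is a slip. The labels are still progression-free rate and survival rate, and the synopsis uses similar labels. A reader might infer that mortality will be reported as survival; with those labels and the correct definitions in section 6.4, that is unlikely. An exact complement also loses no information and causes no bias. This stands too, although the disease progression wording in the Kaplan-Meier paragraph shows that the slip is not confined to one sentence.

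A reader might also infer that the primary analysis censors every discontinuation without progression. For discontinuation itself, the rule is limited to subjects with no later tumour imaging, and other patients continue to be imaged. The conflict remains on either path, because intolerance withdrawal is a PFS event on neither.

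Finally, a treatment-failure composite may have been intended. The document does not say so, and the fix should allow for it. None of these replies explains the added event or the missing death.

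**Conclusion.** Wrong as written and should be fixed, for secondary endpoints only. The intolerance event and the omission of death from DoR are substantive, because they change the quantity estimated and no other part of the protocol resolves them. The event-probability wording is a text correction.

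The intolerance event lowers the 12-month event-free rate by about 2, 4 or 8 percentage points from 39.7% across the assumed 5% to 20% range. This rests on exponential PFS at the planned 9-month median and on independent withdrawal. The withdrawal probabilities are illustrations, not protocol figures. The upward bias in DoR is conditional on deaths in response being censored, and its size is unknown.

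**What to change.** In section 8.2, Analysis of secondary efficacy endpoints:

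1. Replace the definitions with those of section 6.4. State that the 1-year PFS and OS rates are the Kaplan-Meier event-free probabilities at 12 months, read from the PFS and OS curves with the same events and censoring.
2. Remove intolerance withdrawal from the events of the 1-year PFS rate. If a treatment-failure composite was intended, name it as a separate endpoint with its own event definition.
3. End DoR at progression or death.
4. In the Kaplan-Meier paragraph, change the 1-year disease progression rate to the 1-year PFS rate.

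The cost is about five sentences of text. Design, sample size and trial conduct do not change.
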